### Sample size calculation

Calculation of the sample size is based on a reduction in SBP and LDL-cholesterol in the intervention group after 1 year of follow-up. We consider a 5 mmHg absolute reduction in SBP and a 0.3 mmol/L reduction in LDL-cholesterol in the intervention group as clinically relevant [5, 31]. We assume that SBP and LDL-cholesterol levels in the usual care group remain stable. To detect these differences we need a sample size of 370 patients in the intervention group. This calculation is based on an alpha of 0.05, a power of 80%, and an intra-cluster correlation coefficient of 0.05 for the general practice cluster level. Furthermore, we take into account the response rate. We expect that the response rate in the intervention group will be 70%. This results in a sample size of 587 patients in the intervention group. The intervention patients are matched to patients from the usual care group. In the usual care group we estimated a lower response rate of 50%, as these patients might be less used to visit the general practice compared to the probably regularly controlled patients in the intervention group. Therefore, each intervention patient will be matched with 2 patients from the usual care group. This results in 587 × 2 = 1174 patients in the usual care group. The intervention group and usual care group are both divided into two groups (patients with CVD and patients with high CV risk) equal in size. The intervention group is selected from 17 general practices and the usual care group from 9 general practices.

### Statistical analyses

The aim of the main analysis is to compare the SBP and LDL-cholesterol levels after 1 yr of follow-up between patients in the intervention group receiving integrated care for CVRM and the patients in the usual care group receiving usual CVRM care. For the main analysis we will use linear regression. For secondary outcomes, linear regression will be used for continuous outcomes, logistic regression for dichotomous outcomes and multinomial logistic regression for categorical outcomes. All analyses will be corrected for clustering.

Given that patients of clusters of patients are not randomly allocated to the intervention or usual care group, we anticipate that differences in baseline risk might be present between both groups. Hence, we will adjust the analyses for these confounders, including patient characteristics and practice characteristics. To do such adjusted analysis we a priori define the following baseline covariates which are well-known to be related to the outcomes: i) patient characteristics, including relevant medication use, such as blood pressure lowering drugs [32], anticoagulants [33] and lipid lowering drugs [34], relevant comorbidity, including COPD [35], heart failure [36, 37], atrial fibrillation [38], renal failure [39], ii) practice characteristics, such as involved disciplines in CVRM care (including number of PNs) [31], number of patients, and number of GPs. Results will be reported both without (i.e. crude results) and after correction for confounders. Confounders are defined a priori and not selected based on statistical significance.

Furthermore, we will examine whether the effect of the integrated care for CVRM is modified by differences in the following practice characteristics: practice organization (solo/duo/group), availability of CVRM protocol and existence of other disease management programmes (COPD, DM). This will be done by adding interaction effects.

All analyses are applicable to patient data matched on age and gender.

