### Setting

The study is performed in the Zwolle region in the Netherlands. This region includes 56 general practices (solo, duo and group practices) with in total 157 general practitioners (GPs), which are all affiliated to a care group 'Medrie’. Integrated care for CVRM is implemented in this region and coordinated by this care group by providing a practical guideline for the implementation of integrated care for CVRM, offering training to the PNs and organizing yearly benchmark meetings. Furthermore, all general practices collaborate with the same regional hospital (Isala Hospital) with dedicated medical specialists involved in organizing integrated care for CVRM. The care group reached an agreement on integrated care for CVRM with the regionally largest health care insurance company for 3 yrs. Implementation of other disease management programmes e.g. for diabetes mellitus and COPD is also organized by the same care group.

From January 2016, all practices were given the opportunity to participate in the integrated care for CVRM. Every 3 months there was a possibility to start with the programme. Participation was not mandatory. Consequently, the intervention was not randomly allocated to the practices. Prior to our study, approximately two third of the general practices (*n* = 37) chose to implement integrated care for CVRM, while the remaining general practices (*n* = 19) will continue usual care due to a variety of reasons. The practices in the usual care group will not have the opportunity to start with the integrated care for CVRM during the study.

This allowed the opportunity to compare integrated care for CVRM (intervention group) with usual care.

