The endpoint visit consists of the same components as the intake consultation in the integrated programme for CVRM as described before. Data collected during the endpoint visit will be registered in the electronic medical record.

An up-to-date 10-years cardiovascular morbidity or mortality risk will be estimated according to the algorithm of the Dutch national guideline for CVRM. This algorithm is based on the SCORE-function, adapted to the Dutch population and converted from a mortality risk to morbidity and mortality risk (based on the MORGEN-cohort and the Rotterdam Study-cohort) [26–29]. The risk chart takes into account age, sex, smoking status, systolic blood pressure and total cholesterol-HDL cholesterol ratio [23, 24]. For patients taking blood pressure or lipid lowering drugs, the actual SBP and cholesterol levels during treatment are used. For patients with CVD the SMART-function will be used to calculate the CV risk [30]. This function is based on age, sex, smoking status, systolic blood pressure, history of diabetes mellitus, ischemic heart disease, cerebrovascular disease, aortic aneurysm, peripheral arterial disease, time since first diagnosis of CVD, HDL-cholesterol, total cholesterol, renal function (eGFR), and high-sensitivity CRP.

Furthermore, baseline data and data concerning health care use in the past year and in the period prior to the study will be collected by scrutinizing the electronic medical files.

Finally, GPs will be asked to complete a survey about the CVRM care, including questions on the practice setting (rural/urban, solo/group), organization of their practice, availability of trained PNs, CVRM programme and possibilities to refer for lifestyle treatment (social map).

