### Limitations

One limitation is the lack of random allocation to the two arms. This might lead to differences in practice characteristics between the intervention group and the usual group, and lead to either an over- or underestimation of the effect of integrated care for CVRM, when these differences are not adequately adjusted for. Besides, there may be differences in given care before implementation of integrated care for CVRM between different practices within the intervention group. This could also influence the effect of integrated care of CVRM. However, due to the complete registration of patient data in the Dutch general practice information system, we will be able to accurately collect patient data on years prior to the study and take into account the given care prior to the intervention. Furthermore, ample measures have been taken (notably matching of patients, multivariable analyses) to prevent confounding in our study.

Since patients will be selected from different general practices, we have to deal with a cluster effect. The intervention under study may be heterogeneous [40]. For example, differences in practice size, practice facilities and space, training of GP and staff, availability of supportive staff, time-management, attitude towards prevention and the GP-patient relationship might lead to cluster-level differences.

Another limitation of our study design is that it is not possible to blind GPs, PNs and participants for the intervention. Blinding is impossible due to the nature of the intervention. To minimize bias and maximize the validity of the results, participants are selected just before the end of the study. Also, during follow-up the general practices are not informed about which patients are identified as eligible to participate in the study.

A disadvantage of the regional approach of our study is the risk of contamination between the usual care group and the intervention group. Usual care may change in the direction of the intervention and therefore the effect of the intervention may be underestimated. However, as GPs in the usual care group do not use the guideline for the implementation of integrated care for CVRM, do not register patient data in an information system for integrated care, and yearly benchmark meetings are not mandatory, we expect the effect of contamination to be minimal. We will collect data on provided CVRM care to assess contamination.

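### The a priori covariate list does not name baseline SBP or baseline LDL-cholesterol, although 1-year levels are compared between practices that chose their own group

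*Protocol article*

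**What the plan says.** All references are to the protocol article.

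- **Allocation (Setting).** Practices could opt in: "Consequently, the intervention was not randomly allocated to the practices".
- **Primary comparison (Statistical analyses).** "The aim of the main analysis is to compare the SBP and LDL-cholesterol levels after 1 yr of follow-up" between the two groups. The method is also given: "For the main analysis we will use linear regression", with correction for clustering. No change-from-baseline analysis is described.
- **Expected imbalance (same section).** "we anticipate that differences in baseline risk might be present between both groups".
- **Adjustment set (same section).** "To do such adjusted analysis we a priori define the following baseline covariates which are well-known to be related to the outcomes". The patient-level items are blood-pressure-lowering, anticoagulant and lipid-lowering drugs, COPD, heart failure, atrial fibrillation and renal failure. The practice-level items are the disciplines involved (with the number of practice nurses), the number of patients and the number of GPs. Significance testing is ruled out as a way of choosing confounders.
- **Matching (Matching).** Age in 5-year bands, gender and risk group.
- **Sample size (Sample size calculation).** The basis is stated first: "Calculation of the sample size is based on a reduction in SBP and LDL-cholesterol in the intervention group after 1 year of follow-up", with 5 mmHg and 0.3 mmol/L as the relevant effects and usual care assumed not to change.
- **Data (Outcomes and data collection).** "baseline data and data concerning health care use in the past year and in the period prior to the study will be collected" from the electronic files.

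**The concern.** In a non-randomised comparison of follow-up levels, the earlier value of the same outcome is usually the most direct confounder. If practices that joined the programme had patients with lower, or higher, SBP or LDL before the start, part of that difference is still there a year later and is read as a programme effect. The listed covariates are at best indirect markers of the starting level.

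A gap is plausible here. Practices selected themselves. In addition, Usual care group (under Recruitment) lets a usual-care patient with an incomplete risk profile qualify on whatever is recorded, and its example is a known SBP of 160 mmHg. Intervention patients, by contrast, are measured around an intake visit.

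Both primary outcomes are affected. The sample size is framed as a reduction in one group against a stable other group. That equals a difference in 1-year levels only if the groups start equal.

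**Working it through.** **Inputs from the article.** Targets 5 mmHg and 0.3 mmol/L; 370 patients per group; 17 and 9 practices; intra-cluster correlation (ICC) 0.05; alpha 0.05; power 80%. No SD and no baseline-to-1-year correlation are stated.

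**The plan's own figure.** With 370/17 = 21.8 patients per practice, the design effect is 1 + 20.8 × 0.05 = 2.04. For SD 17 mmHg, two-sided alpha and 80% power, n = 2 × (1.960 + 0.842)² × 17²/5² gives 182 per group, and 182 × 2.04 ≈ 371. So 370 is consistent with an SD near 17 mmHg. If each group has its own design effect (2.04, and 3.01 for 370/9 = 41.1 per practice), the implied SD is 15.3 mmHg. With no SD stated, 370 can be neither confirmed nor refuted. The point below does not depend on it.

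**Carry-over.** Suppose the true effect is zero, SDs are equal, and follow-up regresses on baseline with correlation r towards a common mean. A baseline gap d then leaves an expected 1-year difference of r × d when baseline is not in the model. Both r and d are assumptions.

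| Gap d | r = 0.3 | r = 0.5 | r = 0.7 | Share of target |
|---|---|---|---|---|
| SBP 2 mmHg | 0.6 | 1.0 | 1.4 | 12–28% |
| SBP 4 mmHg | 1.2 | 2.0 | 2.8 | 24–56% |
| LDL 0.1 mmol/L | 0.03 | 0.05 | 0.07 | 10–23% |
| LDL 0.3 mmol/L | 0.09 | 0.15 | 0.21 | 30–70% |

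**Do the listed drug covariates absorb it?** This was simulated with 400,000 patients, SD 17, gap 4 mmHg, r = 0.5 and zero effect. Medication use was unrelated, weakly related or more strongly related to baseline SBP (logistic slope 0, 0.03 or 0.06 per mmHg).

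- Crude difference: 1.98 to 2.10 mmHg.
- Adjusted for medication: 1.65 to 2.10 mmHg.
- Adjusted also for baseline SBP: −0.04 to 0.05 mmHg (−0.06 to 0.05 over r = 0.3 to 0.7).

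Medication use removes little of the bias. The measured baseline value removes it under this model.

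**Effect on error rate.** The variance of the contrast is SD² × (2.04 + 3.01)/370, so the standard error is 1.98 mmHg at SD 17 and 1.63 at SD 14. A spurious 2 mmHg difference raises the two-sided 5% false-positive rate to about 17% and 23% respectively.

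**Precision.** In units of SD²/370, the contrast variance is 2.04 + 3.01 ≈ 5.04 (unrounded design effects). The patient-level part is 2 × (1 − 0.05) = 1.90, or 38%. At an assumed r = 0.4 to 0.6, baseline explains r² = 16% to 36% of that part. The gain is therefore 0.38 × 16% ≈ 6% to 0.38 × 36% ≈ 14% of the contrast variance, if baseline explains none of the between-practice variance.

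**The case against.** - **The list is open-ended, and this is a condensed article.** The items are introduced as examples, and a full analysis plan may name the baseline values. This stands in part: a reader might infer that the analysis will exclude them, and the text supports only that it does not name them. But the article does not leave the choice to another document. It presents a referenced set as fixed in advance. A set fixed in advance that leaves the baseline value of each primary outcome to inference lets it be added or dropped once data are seen.
- **The problem is acknowledged elsewhere.** Limitations says, of the time before the programme (the last word is cut here), "we will be able to accurately collect patient data on years prior to the study and take into account the given care prior to the"; both crude and adjusted results are also promised. The commitment there is to prior care, not to the prior level of the outcomes, so it does not close the gap.
- **Any baseline gap passes one-for-one into the result.** A reader might infer this, but it is not established. Under the model above it would need r = 1. It would also happen if each group simply kept its own mean, but the article assumes stability only for usual care, and only for planning.
- **Joining practices already had better values.** This too might be inferred. The article gives only unspecified reasons for not joining, and Limitations allows bias in either direction.
- **The sample size section contradicts the analysis.** It does not. Equal starting levels are a planning assumption.
- **Adjustment is free.** It is not. Usual-care patients have no intake visit, and their blood pressure and lipids may be missing. Recorded values may be high because they led to the patient being classified, which invites regression to the mean. This objection stands and shapes the fix.

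**Conclusion.** The point holds as a gap in the stated adjustment set. The primary analysis compares 1-year levels between self-selected practices and expects baseline differences, yet baseline SBP and LDL-cholesterol are not named, and nothing else in the article makes up for it. The carry-over is about 0.6 to 2.8 mmHg against 5 mmHg, and 0.03 to 0.21 against 0.3 mmol/L. These figures rest on the assumed r = 0.3 to 0.7, gaps of 2 to 4 mmHg and 0.1 to 0.3 mmol/L, and regression to a common mean. The article cannot show whether a gap exists, how large it is or which way it runs.

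Bias reduction is the reason to act; the precision gain of about 6 to 14% is modest. Baseline smoking is also not listed, but it is a secondary matter for SBP and LDL models and the point does not rest on it.

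**What to change.** 1. Name baseline SBP (SBP model) and baseline LDL-cholesterol (LDL model) as covariates in the adjusted primary analysis, added to the existing list.
2. Take the value from the same source in both groups: the last GP-record value within a defined window before t = 0. For usual care, use the intake date of the matched intervention patient. For a randomly invited replacement, use the intake date of the intervention patient whose control is being replaced.
3. Use multiple imputation for missing baseline values, and report by group how many are missing.
4. Add sensitivity analyses: complete cases, and the intake-visit value for the intervention group.
5. Fix this before endpoint data are compared.

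**Cost.** No new patients or visits are needed. The change is mainly analysis wording, plus making sure that dated SBP and LDL values are among the baseline data extracted; the text does not itemise those data, and the figure that may do so is not shown. The real downside is in usual care. Values may be missing more often or recorded selectively, and imputation assumes that missingness is explained by observed data. The report should therefore say that adjustment reduces confounding by starting level but may not remove it.

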### Study procedures

Patients will be identified at the beginning of the study in order to be able to analyse factors such as mortality and comorbidity during follow-up. The study starts when patients in the intervention group visit the general practice for an intake consultation (t = 0). After the intake visit the 1 yr follow-up period commences. After 1 yr of follow-up, patients are invited for an endpoint visit. A questionnaire will be attached to the invitation letter.

Prior to the endpoint visit, all patients who agree with participation in the study will be asked to fill out the questionnaire at home. The timeline of the study procedures is represented in Fig. 1.

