### Outcomes and data collection

An overview of the outcomes of the ZWOT-CASE study is shown in Table 7. The primary outcome is systolic blood pressure and LDL-cholesterol. Patients fill out a questionnaire prior to the endpoint-visit including physical activity (squash questionnaire), quality of life (EQ-5D and SF-12), employment (iPCQ), patient satisfaction regarding the provided care (Patient Reported Experience Measure (PREM)), self-management (Patient Activity Measure (PAM)), and anxiety and depression (Hospital Anxiety and Depression Scale (HADS)). Besides, social status, education (UCC-1 questionnaire) [25], food habits, and CV risk perception are measured by a questionnaire.

**Table 7 Tab7:** Primary and secondary outcomes

Primary endpoints	
1. Systolic blood pressure	
2. LDL-cholesterol	
Secondary endpoints	
1. 10-years cardiovascular morbidity or mortality risk (percentage) (Risk chart Dutch guideline or SMART)	
2. Smoking status	
3. Body mass index (BMI)	
4. Lifestyle (modification) (smoking cessation, healthy food habits, physical activity, motivation for modification and awareness of received advices with respect to weight, food habits and physical activity in the past year)	
5. Awareness of CVD and cardiovascular risk factors	
6. Use of adequate medication (blood pressure lowering drugs, anticoagulants and lipid lowering drugs)	
7. Morbidity (newly developed CVD)	
8. Developed comorbidity (CVD, diabetes mellitus, COPD, heart failure, atrial fibrillation)	
9. Mortality	
10. Primary treating practitioner (GP or medical specialist)	
11. Health care consumption in the past year	
12. Self-management in the past year (patient knowledge, skills, and confidence in managing one’s health and healthcare) (Patient Activity Measure (PAM))	
13. Self-measurements of blood pressure in the past year	
14. Patient satisfaction regarding the provided care in the past year Patient Reported Experience Measure (PREM)	
15. Quality of life (EQ-5D and SF-12)	
16. Anxiety and depression (Hospital Anxiety and Depression Scale (HADS)	
17. Cost-efficiency (iPCQ)	

* HIS = general practice information system

Further, a blood sample is taken for measurement of lipids (total cholesterol, HDL-cholesterol, TC/HDL-cholesterol ratio, LDL-cholesterol, triglycerides), renal function (creatinine, MDRD), glucose and for patients with CVD hs-CRP.

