### Strengths

First, the pragmatic design of the ZWOT-CASE study will give insight into whether integrated care for CVRM compared to usual care is effective in a real world environment. If integrated care for CVRM has a positive effect on our outcomes, it supports the idea that the intervention is beneficial in daily practice.

Furthermore, all the general practices are affiliated to the care group ‘Medrie’. The regional implementation of integrated care for CVRM will lead to a more uniform intervention and to less differences between general practices in the intervention group and consequently to less between-cluster variability. Also, the care group reached an agreement on integrated care for CVRM with the health care insurance for the coming 3 yrs, ensuring an adequately financed and stable health care environment during the follow-up of the ZWOT-CASE study. GPs in the usual care group are also members of the care group. This makes the usual care group probably more comparable with the intervention group with regard to socioeconomic characteristics and available opportunities for referrals.

Finally, a strength of the ZWOT-CASE study is the lenient inclusion criteria, i.e. patients with a CV risk of > 10%. Since usually more strict inclusion criteria are used in other regions, subgroup analysis will enable us to translate our results to other regions.

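### Education is collected but not named among the a priori covariates, although the questionnaire outcomes have no baseline score in either arm

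*Protocol article*

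**What the plan says.** Statistical analyses, in the protocol article, presents the adjustment set as fixed beforehand: "we a priori define the following baseline covariates which are well-known to be related to the outcomes". At patient level it names "patient characteristics, including relevant medication use, such as blood pressure lowering drugs", then anticoagulants and lipid lowering drugs, and four comorbidities (COPD, heart failure, atrial fibrillation, renal failure). At practice level it names "practice characteristics, such as involved disciplines in CVRM care (including number of PNs) [31], number of patients, and number of GPs". One set serves all adjusted analyses; none is given separately for the questionnaire outcomes.

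Outcomes and data collection says that "social status, education (UCC-1 questionnaire) [25], food habits, and CV risk perception are measured by a questionnaire". On timing, Study procedures places the questionnaire with the invitation to the endpoint visit, after one year: "A questionnaire will be attached to the invitation letter". Ethical aspects and informed consent adds that neither arm has a study baseline visit, that patients do not know of the study at baseline, and that baseline data are gathered retrospectively.

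Matching uses age in 5-year categories, gender and risk group. Strengths remarks, of the usual-care GPs belonging to the same care group, "This makes the usual care group probably more comparable with the intervention group with regard to socioeconomic characteristics".

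**The concern.** Practices chose whether to join the programme, so the arms may differ in ways unrelated to it. For SBP and LDL-cholesterol, earlier values may be found in the medical records. For PAM, PREM, EQ-5D, SF-12, HADS and SQUASH there is no earlier score in either arm, so a pre-existing difference cannot be seen or removed through the outcome itself. What remains is matching on three factors and the named covariates, which at patient level are clinical. Education may plausibly be related to self-management, satisfaction, quality of life and lifestyle, and nothing named stands in for it directly.

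At stake is whether a difference in questionnaire scores between arms can be read as a programme effect, or whether part of it reflects who attends, and who responds in, the two sets of practices.

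**Working it through.** The plan states no figure on this point, so there is none to reproduce. The check has a textual part and an illustration of scale.

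**Text**

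1. *Is the covariate set fixed here?* Yes. Statistical analyses lists it and says confounders are defined a priori and not selected on statistical significance.
2. *Is a socioeconomic variable named?* No, at neither patient nor practice level.
3. *Is one available at no extra cost?* Yes. Education and social status are in the endpoint questionnaire (Outcomes and data collection).
4. *Can education serve as a baseline covariate although it is asked at the end?* Yes. At ages 40–80 it hardly changes in a year and cannot sensibly be a result of the programme. Social status is less safe, because it is measured after a year of exposure.
5. *Do the questionnaire instruments have a baseline?* No. They are sent once, with the endpoint invitation (Study procedures), and patients are not approached at baseline (Ethical aspects and informed consent).
6. *Is imbalance plausible on the document's own account?* Yes. Allocation was by practice choice (Setting). Of 37 programme and 19 usual-care practices, 17 and 9 took part (Setting; Recruitment of patients). Expected response is 70% versus 50% (Sample size calculation). Programme patients are approached around a routine yearly visit, usual-care patients by letter and telephone with replacement of refusers (Recruitment of patients).

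**Scale**

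Inputs from the document: 370 patients per arm, 17 and 9 practices, ICC 0.05, alpha 0.05 (taken as two-sided; the article does not say), and a relevant SBP difference of 5 mmHg.

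Inputs assumed, because the document gives none: low education differs between arms by 5–20 percentage points. Low versus higher education shifts a questionnaire score by 0.2–0.5 SD, or SBP by 2–6 mmHg.

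*Standard error of a standardised difference*, with design effect DE = 1 + (m − 1) × ICC:

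- Intervention: m = 370/17 = 21.8; DE = 1 + 20.8 × 0.05 = 2.04
- Usual care: m = 370/9 = 41.1; DE = 1 + 40.1 × 0.05 = 3.01
- SE = √((2.04 + 3.01)/370) = 0.117 SD

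*Bias = imbalance × gradient.* The last column is the chance of |Z + bias/SE| exceeding 1.96 when there is no true effect.

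| Imbalance | Gradient (SD) | Bias (SD) | Bias/SE | Two-sided type I error |
|---|---|---|---|---|
| 0.05 | 0.2 | 0.010 | 0.09 | 5.1% |
| 0.10 | 0.3 | 0.030 | 0.26 | 5.8% |
| 0.10 | 0.5 | 0.050 | 0.43 | 7.1% |
| 0.20 | 0.3 | 0.060 | 0.51 | 8.1% |
| 0.20 | 0.5 | 0.100 | 0.86 | 13.7% |

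*SBP:* 0.05 × 2 = 0.1 mmHg to 0.20 × 6 = 1.2 mmHg, or 2% to 24% of 5 mmHg. The middle case, 0.10 × 4 = 0.4 mmHg, is 8%.

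**The case against.** The strongest reply is that the list is worded openly. The patient characteristics are introduced as examples, and a journal article may leave the complete list to a fuller document. This stands in part: education is not excluded, and a reader who infers that the authors decided against it goes beyond the text. But the same paragraph rests its credibility on confounders being defined beforehand, and a covariate that is not named is not pre-specified.

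A reader might also infer that the covariates are the only protection against confounding. They are not. Patients are matched, and Limitations plans to use records from before the study to account for prior care. Neither supplies socioeconomic information or a baseline questionnaire score.

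Nor is it right that nothing self-reported exists at baseline. Table 5 shows smoking, dietary habits, alcohol and activity days assessed at the programme intake. That covers the intervention arm only; Usual care group, under recruitment, says there is no such intake there and that smoking status may be missing. The absence of a baseline in both arms is exact only for the questionnaire instruments.

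The remark in Strengths might be read as the reason for leaving education out. It is a hedged, relative statement in the Discussion, and nothing in the article uses it that way. Limitations openly says that inadequate adjustment could bias the result in either direction.

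Finally, the size is wholly assumed. The low end is negligible and the high end needs both assumptions at their maximum. The formula uses a crude gradient, part of which the planned covariates may already absorb. The article attributes the lower usual-care response to patients being less used to visiting the practice; that this alters the educational mix is plausible but not shown. All of this stands.

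**Conclusion.** The point holds in a limited form. The article fixes an a priori adjustment set that names no socioeconomic variable, although it collects education and compares self-selected practices on instruments with no baseline score. A socioeconomic difference between arms would stay in the adjusted estimates.

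Neither the size nor the direction of the bias can be derived from the documents. Under the stated assumptions it is 0.01–0.10 SD for a questionnaire score, that is 0.09–0.86 standard errors, and the nominal 5% error rate becomes 5.1–13.7%. For SBP most of the range is small against 5 mmHg. The concern therefore bears mainly on the patient-reported secondary outcomes and only to a lesser extent on smoking, SBP and LDL-cholesterol. It does not show that the primary comparison is invalid. The change is worth making because it removes a plausible source of confounding with data the study already collects.

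**What to change.** In Statistical analyses, name education level among the a priori patient characteristics for the adjusted models. State that missing education values will be imputed, so that a patient who attended the endpoint visit but left the item blank is not dropped from the SBP and LDL-cholesterol models.

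Use social status only in a sensitivity analysis, since it is measured after a year of exposure and the plan calls for baseline covariates.

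Report education by arm in the results publication, where the remark on socioeconomic comparability can be checked. Such a table cannot stand in a design paper written before the data.

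No new data collection is needed. The cost is a few patient-level degrees of freedom and the need to specify how missing questionnaire items are handled.
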